#### Sample size estimation

We powered this phase II trial based upon the primary outcome. Using data from the Alberta Cancer Registry, Martin and colleagues described a standard deviation of MA at 8.6 Hounsfield units (HU) for males and 10.2 HU for females [20]. We therefore assumed an overall mean SD of 9.4 HU for both male and female patients. A difference in MA between groups of 8HU was considered to be of clinical importance, and the calculation was based on showing a difference of this size between groups.

The proposed analysis will adjust the differences at 6 months for the MA values at baseline. To allow for this approach, this adjusted is included in the sample size calculation. The size of the association between baseline and outcome MA values is relatively unknown. A fairly weak correlation of about 0.3 between the time points was assumed.

The calculations were performed using a 5% significance level and 90% power. Based on the information above, it was calculated that to show a difference in MA of 8 units between groups would require a sample size of 27 per group (54 patients in total).

To allow for an estimated dropout rate of 5%, 58 patients will be recruited into the study. The dropout rate of 5% is an estimate based on the fact that the treatment period is short and supervised for the most part in hospital. For the primary outcome to be measured, we require the pre- and post-operative CT scans and therefore anticipate a very low dropout rate due to the fact these are routine scans and the time period is relatively short. The dropout rate for the secondary outcomes may be higher as the time from surgery progresses; however, the trial is powered to the primary outcome and as such, we are not taking into account the potential drop out from the trial outside this time period encompassing the primary outcome metrics.

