#### Data collection

Surveillance CT scans performed as part of sequential screening (i.e. not emergency or non-routine imaging) are performed as standard in this patient group and will undergo analysis measuring mean muscle attenuation (myosteatosis) and muscle area (sarcopenia) at the level of the third lumbar vertebrate. Routine bloods including CEA (carcinoembryonic antigen) and inflammatory markers will be measured at each elective routine clinic visit and these data recorded, these samples will be collected, analysed and disposed of in accordance with the LNWH NHS Trust policy. Quality of life will be assessed at 6 and 12 months using validated quality of life questionnaires (ED-5Q-5L & EORTC QLQ – CR29). The Berg Balance scale, 30-s sit-to-stand test and 6-min walk test [21–24] will be used to assess functional outcome these tests will be performed at the patients 3 months post operatively clinic appointment. Pre- and post-operatively, we will measure bilateral thigh circumference at 15cm above the superior pole of the patella (which has been shown in earlier studies to correlate with muscle volume on MRI) [25]. Bio-impedance analysis (BIA) will be undertaken at baseline, day 2 post-operatively, day 28 post-operatively (if in hospital), day of discharge and first post-operative follow-up appointment. We will record data from the device satisfaction questionnaires from both groups. Standard outcome data and covariates to be collected are shown in Table 4.

**Table 4 Tab4:** Outcomes and covariates

**Demographics** o Patient age o Patent birth year o Patient gender o Patient ethnicity coding o Weight o Height o Body mass index	**Outcome measures** o 90-day post-operative complications (Clavien-Dindo classification (18)) o Disease outcomes including 30-day survival o Death / recurrence / disease-free survival o Patient compliance diary data o Device usage
**Disease** o ASA grade (American College of Anaesthesiology) physical status o Past medical history (other or previous illnesses and surgery)	**Body composition parameters** o CT body composition at the level of the L3 vertebra o Bio-impedance analysis o Anthropometric measurements
**Cancer-specific characteristics** o Type of cancer (primary/recurrent cancer, location and subtype on histology) o Grade of cancer o Stage of cancer	**Inflammatory markers** o Serum C-reactive protein o White cell count o Serum albumin o Platelet count

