### Planned statistical analyses

This study will be performed in line with the CONSORT criteria (http://www.consort-statement.org/consort-2010). Initially outliers, patterns of attrition and missing data will be identified using a combination of graphical displays and descriptive statistics allowing decisions on the assumption of normality. The primary analysis will be of observed data only, with patients with missing data omitted from the analysis. If the primary outcome has >10% missing data points, a sensitivity analysis will be performed using multiple imputation to estimate the missing values.

Data will be analysed by a statistician blinded to the intervention. Analyses of primary and secondary endpoints will be based on the full analysis set defined according to the intention to treat principle. Safety analysis will be performed for the on all enrolled individuals with disclosure of any significant adverse events. The full analysis set consists of all participants consented and randomised with valid baseline assessments. Participants will be analysed according to the study arm they were assigned at randomisation.

The primary outcome is myosteatosis at 3–6 months post-surgery, derived from the mean muscle attenuation on CT body composition analysis. This will be analysed using analysis of covariance (ANCOVA), with muscle attenuation values at baseline used as a covariate in the analysis.

The secondary outcome measures measured on a continuous scale, and with a baseline measurement will be analysed using equivalent methods as the primary outcome. For continuous outcomes with no baseline measurement, group comparisons will be made using either the unpaired *t*-test or Mann-Whitney test, depending on data distribution. The chi-square test, or Fisher’s exact test, will be used to compare categorical outcomes between the study groups.

Significance will be assumed when *p*<0.05.

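### The planning SD is an average of within-sex SDs, but the primary ANCOVA does not adjust for sex; if the sexes differ in mean muscle attenuation, power is somewhat lower than planned

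*Protocol article*

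**What the plan says.** Under Sample size estimation, the protocol article cites a cancer registry study that "described a standard deviation of MA at 8.6 Hounsfield units (HU) for males and 10.2 HU for females". From these two values it takes a single planning figure: "We therefore assumed an overall mean SD of 9.4 HU for both male and female patients". The other inputs are the target effect ("A difference in MA between groups of 8HU was considered to be of clinical importance"), the link between baseline and follow-up ("A fairly weak correlation of about 0.3 between the time points was assumed") and the error rates ("The calculations were performed using a 5% significance level and 90% power"). The result is 27 per group, or 58 patients in total after a 5% dropout allowance.

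Under Planned statistical analyses, the primary model is given in one sentence: "This will be analysed using analysis of covariance (ANCOVA), with muscle attenuation values at baseline used as a covariate in the analysis". No other covariate is named for the primary outcome.

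Table 3 admits both sexes. Table 4, under Data collection, lists "Patient gender" among the demographics. The Randomisation section mentions no stratification by sex. The article gives no mean MA by sex and no expected sex mix, and it does not say whether 0.3 is a correlation within sex or over both sexes together.

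**The concern.** The variance of a mixed-sex sample has two parts: the variance within each sex, and a term for the distance between the male and female means. Averaging two sex-specific SDs keeps the first part and drops the second. That suits an analysis that removes the mean difference between the sexes, and the stated model does so only indirectly, through baseline MA. With a weak assumed correlation, the baseline covariate carries only part of a sex difference.

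At stake is precision. If the sexes differ in mean MA, the residual SD of the stated analysis exceeds the value behind the 27 per group, and power is below plan. The size of the loss depends on a male-female difference that the article does not give.

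**Working it through.** **Reproducing the plan's figure.** Inputs from Sample size estimation: SD 9.4 = (8.6 + 10.2)/2, effect 8 HU, correlation 0.3, 5% significance (taken as two-sided, since the article does not say and two-sided reproduces the figure), 90% power.

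- Residual SD = 9.4 × √(1 − 0.3²) = 8.97 HU.
- n per group = 2 × (1.960 + 1.282)² × 8.97² / 8² = 26.4, rounded up to 27.
- 27/0.95 = 28.4, rounded up to 29 per group, or 58 in total.

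Both stated figures are reproduced.

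**What the average leaves out.** Let d be the male-female difference in mean MA and p the proportion of men. Then total variance = within-sex variance + p(1 − p)d². I assume p = 0.5, so the second term is d²/4. The within-sex variance is (8.6² + 10.2²)/2 = (73.96 + 104.04)/2 = 89.0, an SD of 9.43. That is nearly the same as 9.4 and also gives 27 per group. Since d is not in the documents, I assume 4, 6 and 8 HU:

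- d = 4: √(89 + 4) = 9.64 HU
- d = 6: √(89 + 9) = 9.90 HU
- d = 8: √(89 + 16) = 10.25 HU

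**How much baseline MA absorbs.** This depends on what 0.3 refers to. Both readings assume the same sex difference at baseline and at follow-up.

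*Reading 1: 0.3 is the within-sex correlation.* The overall correlation is (0.3 × 89 + d²/4)/(89 + d²/4) = 0.33, 0.36 and 0.41. The residual SD without sex is total SD × √(1 − overall correlation²). With sex in the model it is 9.43 × √0.91 = 9.00, whatever d is.

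*Reading 2: 0.3 is the overall correlation.* The residual SD without sex is total SD × √0.91. The implied within-sex correlation is (0.3 × total variance − d²/4)/89 = 0.27, 0.23 and 0.17, so the residual SD with sex is 9.43 × √(1 − within-sex correlation²).

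**Power** by noncentral t, 27 per arm, effect 8 HU, noncentrality 8/(residual SD × √(2/27)), with 51 degrees of freedom without sex and 50 with it:

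| d (HU) | Reading | Residual SD without sex | Power without sex | Residual SD with sex | Power with sex |
|---|---|---|---|---|---|
| 4 | 1 | 9.10 | 88.6% | 9.00 | 89.3% |
| 6 | 1 | 9.22 | 87.9% | 9.00 | 89.3% |
| 8 | 1 | 9.36 | 86.9% | 9.00 | 89.3% |
| 4 | 2 | 9.20 | 88.0% | 9.09 | 88.7% |
| 6 | 2 | 9.44 | 86.3% | 9.18 | 88.1% |
| 8 | 2 | 9.77 | 83.9% | 9.29 | 87.3% |

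**Cost when there is no sex difference.** At d = 0, power is 89.33% without sex and 89.30% with it.

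**The gap to 90%.** Part of it is a matter of method. The plan's normal formula gives 90.6% at 27 per group with SD 9.4; the noncentral t gives 89.5% for the same inputs and 89.3% with SD 9.43. That step of about one point has nothing to do with sex, so only the differences between columns bear on this point.

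**The case against.** A reader might infer that all between-sex variation stays in the error term and that the stated precision is therefore wrong. The documents do not support that. They report no mean MA by sex, so d could be small; on the normal formula, a difference of up to 5 HU raises the requirement to at most 29 per group. Baseline MA also carries any sex difference already present at baseline. And 27 per group follows correctly from the stated inputs.

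It is also tempting to say that adding sex always restores power to 89%. That holds only if 0.3 is the within-sex correlation. On the other reading, power with sex is 88.7%, 88.1% or 87.3%.

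Nor is chance sex imbalance a separate harm. Its effect is already in the variance used above, and randomisation protects against bias.

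Further, ANCOVA with one covariate is a valid primary analysis, and the article openly describes the baseline-outcome association as largely unknown. If the within-sex correlation were 0.5 (an assumption), power without sex would be 93% even at d = 8. The article is condensed, and the full protocol or an analysis plan may name more covariates.

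All of this limits the size of the point. What remains is a mismatch between two things the article does state: the basis of the SD and the primary model.

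**Conclusion.** The point holds as a minor one about precision. The planning SD is a within-sex average, and the stated primary model does not adjust for sex. If the sexes differ in mean MA by 4 to 8 HU, adding sex gains about 0.7 to 2.4 percentage points of power when 0.3 is the within-sex correlation, and about 0.7 to 3.5 points when 0.3 is the overall correlation and the sex difference persists. With no sex difference, nothing is gained and almost nothing is lost. These sizes rest on an assumed d, an equal sex mix and 27 analysed per arm. There is no arithmetic error in the sample size and no bias in the treatment comparison.

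**What to change.** In Planned statistical analyses, name sex as a covariate alongside baseline MA in the primary ANCOVA. In Sample size estimation, state that 9.4 HU is a within-sex SD, and say whether 0.3 is meant within sex or overall. If the sponsor prefers to keep the single-covariate model, the consistent alternative is to base the calculation on a justified mixed-sex SD.

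The cost is one of 51 residual degrees of freedom, about 0.03 percentage points of power when the sexes do not differ. No new data are needed, and the planned number of patients need not change. The calculations cover the primary outcome only, so they are no argument for changing the secondary CT outcomes.

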### Trial protocol

#### Recruitment and eligibility screening

The inclusion and exclusion criteria are shown in Table 3. Following diagnosis of locally advanced rectal cancer patients is discussed in a multidisciplinary team (MDT) meeting. Some of these patients may be felt to be suitable for radical surgery—i.e., surgery performed with the intention of a cure. If patients are deemed fit for and consent to surgery then this is performed by one of three specialist surgeons in St Mark’s Hospital, London, UK.

**Table 3 Tab3:** Inclusion and exclusion criteria

Inclusion criteria	Exclusion criteria
○ Adults age 18 and above ○ Male or female ○ Primary or recurrent locally advanced rectal cancer amenable to elective radical exenterative surgery ○ ASA grades I–III ○ Able and willing to consent ○ in other concurrent trials is acceptable—following discussion with trial team of both studies	○ Lack of patient consent ○ Widespread metastases not amenable to curative resection ○ Contraindication to NMES ○ Pre-existing neuromuscular degenerative disease ○ Participation in other trials where agreement on participation not made in advance by trial teams ○ Patients with solitary colon cancer above the level of the peritoneal reflexion which does not require complex pelvic surgery

Patients who meet the inclusion criteria will be identified by the clinical team in the colorectal outpatient clinic or MDT and will then be approached by the study team with written information on the trial and given the option to enrol in the study. Consent to take part in the trial will be obtained at the next outpatient clinic appointment, which will occur in the weeks preceding surgery. Patients may be included in concomitant studies; provided agreement is obtained from each trial team. Further details regarding recruitment the strategy can be found on pages 21–22 of the Full Protocol (Supplementary Material).

Detailed information on participant withdrawal and discontinuation is provided on page 22 of the full protocol and within the consent and participant information sheet (supplementary material).

#### Randomisation

Randomisation, performed after the assessment of baseline outcomes, will take place by computer-generated randomisation software (https://www.sealedenvelope.com) on a one-to-one basis. Recruitment will be performed by the study team; randomisation will be performed by the study principal investigator. Patients who are randomised to the either arm will be blinded as to intervention and will be taught by the research team to use the stimulator; this will be at their clinic appointment following consent.

The NMES intervention lasts a total of 10 weeks with follow-up over 5 years. The trial algorithm is shown in Fig. 1 and schedule of enrolment, interventions and assessments in Fig. 2.

**Fig. 1 Fig1:**
[figure not shown]
Study algorithm

**Fig. 2 Fig2:**
[figure not shown]
Schedule of enrolment, interventions and assessments

#### Blinding

Patients and the assessor of the primary outcome will be blinded. Patients will be blinded as to which arm they are in; the devices appear identical with the exception of a small, coloured plastic tab indicating whether they are treatment or placebo devices. The assessor of the primary outcome, a consultant radiologist, will be blinded as to which trial arm the participant is in; assessment of the primary outcome is also automated and therefore will not allow bias. The clinical team caring for the participant will not be aware of which trial arm the patient is in. It is not possible for the individuals providing the NMES therapy to be blinded as they will need to be aware of which arm the patient is in in order to provide effective advice.

#### Data collection

Surveillance CT scans performed as part of sequential screening (i.e. not emergency or non-routine imaging) are performed as standard in this patient group and will undergo analysis measuring mean muscle attenuation (myosteatosis) and muscle area (sarcopenia) at the level of the third lumbar vertebrate. Routine bloods including CEA (carcinoembryonic antigen) and inflammatory markers will be measured at each elective routine clinic visit and these data recorded, these samples will be collected, analysed and disposed of in accordance with the LNWH NHS Trust policy. Quality of life will be assessed at 6 and 12 months using validated quality of life questionnaires (ED-5Q-5L & EORTC QLQ – CR29). The Berg Balance scale, 30-s sit-to-stand test and 6-min walk test [21–24] will be used to assess functional outcome these tests will be performed at the patients 3 months post operatively clinic appointment. Pre- and post-operatively, we will measure bilateral thigh circumference at 15cm above the superior pole of the patella (which has been shown in earlier studies to correlate with muscle volume on MRI) [25]. Bio-impedance analysis (BIA) will be undertaken at baseline, day 2 post-operatively, day 28 post-operatively (if in hospital), day of discharge and first post-operative follow-up appointment. We will record data from the device satisfaction questionnaires from both groups. Standard outcome data and covariates to be collected are shown in Table 4.

**Table 4 Tab4:** Outcomes and covariates

**Demographics** o Patient age o Patent birth year o Patient gender o Patient ethnicity coding o Weight o Height o Body mass index	**Outcome measures** o 90-day post-operative complications (Clavien-Dindo classification (18)) o Disease outcomes including 30-day survival o Death / recurrence / disease-free survival o Patient compliance diary data o Device usage
**Disease** o ASA grade (American College of Anaesthesiology) physical status o Past medical history (other or previous illnesses and surgery)	**Body composition parameters** o CT body composition at the level of the L3 vertebra o Bio-impedance analysis o Anthropometric measurements
**Cancer-specific characteristics** o Type of cancer (primary/recurrent cancer, location and subtype on histology) o Grade of cancer o Stage of cancer	**Inflammatory markers** o Serum C-reactive protein o White cell count o Serum albumin o Platelet count
**Treatment factors** o Details of surgery o Chemotherapy o Radiotherapy	**Patient-specific and functional outcomes** o Quality of life - ED-5Q-5L - EORTC QLQ – CR29 o Patient satisfaction

Data collection will be undertaken using a case report form (CRF) designed by the investigators; the data will be transferred from the CRF to a Microsoft Excel Database *(Microsoft Corporation, Redmond, Washington, USA)*, stored in the LNWH NHS Trust secure network. All collected data will be reviewed by the principal investigator prior to analysis and specific searches on written notes or electronic record systems will be made to address any missing data points. The data collected as part of this trial will be subject to review by the independent Trial Data Monitoring committee on request as per the Data Monitoring Charter (supplementary material).”

Information on data management, storage and curation is available in the Full Trial Protocol (supplementary material, page 17).

#### Data monitoring and compliance

A sponsor-approved independent data monitoring committee (IDMC) has been appointed to the trial as part of good trial governance to ensure safety, scientific validity and integrity of the trial. The data monitoring committee will have access to raw data and will review any significant adverse events or safety concerns within the trial. The IMDC will make recommendations and report directly to the sponsor representative and chief investigator. The trial Data Monitoring Charter is included for review within the supplementary material. Further information on data management and security and storage are available in the Full Protocol, supplementary material pages 17, 26 and appendix 4.

### Study intervention

#### Stimulation of muscle

We will endeavour to stimulate two major muscle groups during the study, the quadricep muscles and paraspinal muscles. The muscles of the quadriceps, particularly vastus lateralis and vastus medialis, will be stimulated in both legs; this will be performed with a view to preserving muscle mass and encouraging earlier ambulation and better function.

We will also stimulate the erector spinae muscles and the muscles of the lower back. The reason for this is twofold: firstly, it is felt that some of the earliest muscles to atrophy following surgery or during bed rest are the core muscles of the back especially as these patients will not be sitting up or utilising these important supportive muscles in the first stages of their recovery. Patients are nursed on their side during the first 14 days following major pelvic surgery, which means they tend not to use their core muscles to flex or extend their back or support their weight leading to loss. This lateral position however would afford easy access to place the electrodes. Secondly, we are focussing on the muscle groups at the third lumbar vertebrate—the level this stimulation would take place, using the device in this location, would give us the best chance of demonstrating the benefits of the device with regard to muscle preservation. This site is well away from the operative site and tumour bed in these individuals and therefore there would be no risk of stimulating the tumour bed whilst using the device in this position.

Neuro-muscular stimulation will be delivered by a *MicroStim Exercise Stimulator* MS2v2 (*Odstock Medical Limited (OML), Wiltshire, UK*) using two self-adhesive electrodes placed on the anterior thigh over the body of the vastus medialis and lateralis and the muscles of the lower back. At their second clinic appointment at St Mark’s, patients will be trained by the research fellow or other competent research team member (physiotherapist or specialist nurse) to use the NMES. A study-specific instruction leaflet will be given to this group along with the standard instruction manual by OML.

#### Intervention training

Training in using the MicroStim 2v2 has been undertaken by the trial principal investigator at the device manufacturer, OML. Patient training will be conducted by the study PI or a trained member of their study team. Patients using the device will be observed and educated on correct usage by the study team. They will be asked to keep a usage diary and the device will record usage statistics via an inbuilt recorder. These data will feed into the analysis to provide a dose response model within the final analysis.

